In studies examining the impact of DSME on mortality, most (*n* = 28) cite mortality as a reason for drop‐out rather than examining mortality as a primary outcome measure,^13^, ^16^, ^17^, ^18^ and only two studies report significant improvements following DSME.^13^, ^16^ In a study from Hong Kong, attending one or more DSME sessions was associated with lower all‐cause mortality (HR:0.59, CI 95% 0.632–0.968, *p* = 0.024); however, differences existed between study groups,^13^ with similar findings described in a UK randomised control trial, where mortality in participants requiring ambulance transfer for severe hypoglycaemia was 33.3% in those that had attended DSME compared with 51.2% in those receiving standard care without DSME (HR 0.65, *p* = 0.025).^16^ DSME workshops for an elderly Argentinian type 2 cohort resulted in an 33% lower 6‐year crude mortality rate, but significance was lost in multivariate analysis showing only a weak (18%) association between DSME attendance and reduced mortality (HR 0.82; 95%CI: 0.61–1.08) but socio‐economic data was not reported as a confounder, and those in the non‐attendance group had an increased stroke prevalence, higher diastolic blood pressure and LDL‐C which could explain the increased mortality rate.^17^ This weak association between DSME attendance and mortality was also reported in an earlier study which simulated the long‐term cost‐effectiveness of DSME interventions over 20 years, however, results obtained in this simulated RCT may not be representative of diabetes care delivered outside of this type of clinical trial.^18^

In short, existing studies provide evidence that DSME improves well‐being, self‐management skills and short‐term blood sugar control (HbA1c), but crucially evidence of an impact of DSME on hospital admissions and premature mortality is limited and conflicting and has not been assessed in a real world setting on this scale.

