## AIMS AND OBJECTIVES

2

The aim of this large retrospective cohort study is to examine the impact of DSME attendance on all‐cause and cause‐specific hospital admissions and mortality in people with type 2 diabetes, utilising linked large UK national datasets to test the hypotheses that DSME attendance impacts all‐cause hospital admissions and mortality.

The specific objectives are to:To describe the epidemiology of patients living with type 2 diabetes who have attended DSME by age, sex, ethnicity, deprivation levels (IMD), HbA1c and baseline Charlson Comorbidity Index in a representative sample of a large cohort of adults who were registered with an English GP between 2011 and 2021.To examine the association between ever or never having attended DSME on all‐cause and cause‐specific hospital admissions, in adults with type 2 diabetes.To examine the association between ever or never having attended DSME on all‐cause and cause‐specific mortality, including but not confined to in‐hospital mortality.To examine the association between ever or never having attended DSME on major adverse cardiovascular events (3P‐MACE); CV death, non‐fatal myocardial infarction (MI) and non‐fatal stroke, in adults with type 2 diabetes.

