### Data processing and analysis

3.4

To increase the efficiency of clinical trials researchers embarking on prospective longitudinal studies will often include restrictive eligibility criteria to restrict potential mortality from existing comorbid conditions.^22^ Such restrictions in retrospective studies limit generalisability of the findings and result in significant loss of individuals included in the study. An alternative approach introduced by Charlson^22^ classifies patients with comorbid disease according to their risk of death from disease at entry to a study, allowing researchers to classify the risk of one‐year and 10‐year mortality.^22^, ^31^ Charlson Comorbidity Index (CCI) can be classified as mild (1–2), moderate (3–4) and severe (≥5).^25^ With each increased level of the comorbidity index, there is a stepwise increase in the cumulative mortality attributable to comorbid disease.^22^ CCI will be calculated from CPRD Aurum to predict a patient's 10‐year risk of mortality and managed as a confounding factor during multivariate analysis.

Not all aspects of health data are captured in CPRD, for example, socio‐economic demographics which are an independent effect modifier contributing to increased mortality in people with type 2 diabetes, with mortality risk increased in those in the most deprived neighbourhoods by as much as 11% per quintile of deprivation where the person also had a diabetic foot ulcer.^32^ Linkage to patient level indices of multiple deprivation (IMD) deciles will overcome this. IMD will be managed as a cofounding factor during multivariate analysis and this limitation will need to be addressed fully in our discussion.

We will use primary care demographic data and READ codes for CPRD Aurum and laboratory tests to confirm main potential confounders at baseline. These include age, sex, time since first use of diagnosis code (as a proxy for diabetes duration and age at diagnosis in years), multimorbidity (CCI), BMI, smoking status and laboratory results for HbA1c, systolic blood pressure (SBP) and total cholesterol. Ethnicity and patient level IMD will be included following linkages with relevant health datasets.

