### Statistical methods

3.6

Baseline characteristics of participants will be summarised using descriptive statistics (mean, median, interquartile range and standard deviations as appropriate). We will also summarise total number of hospital admissions and length of stay by age, age at time of diabetes diagnosis, diabetes duration, ethnicity and IMD decile.

The primary cohort is those who have ‘*ever*’ received DSME in each of the 10 years in the study to identify hospital admissions and cause of death during follow‐up. We will additionally have a matched diabetes cohort who have ‘*never’* received DSME to provide comparison (rate ratios).

An initial crude analysis will compare the proportion of hospitalisations and deaths between *ever* and *never* DSME groups. Chi‐squared tests will be used to compare these proportions. Similar tests will be used for subgroup analysis and alternative outcomes (cause‐specific hospitalisations and mortality).

Number of hospital admissions will be calculated to estimate relative risk of admissions and mortality by all‐cause and cause‐specific using a mixed Poisson model. Should the data be over dispersed a negative binomial mixed model will be adopted.

A Cox proportional‐hazards model will be used to measure time to event for first hospital admissions and mortality with the proportional hazards assumption checked using Kaplan—Meier curve plots and Schoenfeld residuals tests. If the proportional hazards assumption does not hold, then alternatives such as restricted mean survival times models will be used.

Baseline covariates will be reported among the ‘ever’ and ‘never’ groups, and a statistical test will be applied to see whether these differ significantly. These will be examined in multivariate models. We will address potential issues with confounding by indication firstly within the study design in which individuals in the ever group will be matched at baseline for age, sex, diabetes duration and age at diagnosis to individuals in the never group. All models will be adjusted a priori for CCI, IMD, HbA1c, BMI, smoking status, lipid level and SBP during multivariate analysis.

Statistical analysis will be conducted using R version 4.4.1. Alpha level will be set at 5% for statistical significance.

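### Adjusting comorbidity only through a summed mortality score may leave 3P-MACE and cause-specific models confounded by history of the same disease

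*Protocol article*

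**What the plan says.** Section 3.6 (Statistical methods) states: "All models will be adjusted a priori for CCI, IMD, HbA1c, BMI, smoking status, lipid level and SBP during multivariate analysis". Section 3.4 (Data processing and analysis) explains the comorbidity term: "CCI will be calculated from CPRD Aurum to predict a" patient's 10-year "risk of mortality and managed as a confounding factor during multivariate analysis". The list of main confounders in the same section names comorbidity only in this form: "multimorbidity (CCI), BMI, smoking status and laboratory results for HbA1c, systolic blood pressure (SBP) and total cholesterol".

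Nothing else in the design handles disease history. Patients in the ever group are "matched at baseline for age, sex, diabetes duration and age at diagnosis to individuals in the never group". Section 3.4 argues against restricting entry by comorbidity ("Such restrictions in retrospective studies limit generalisability of the findings and result in significant loss of individuals included in the study") and offers CCI as the alternative.

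The same covariate set serves outcomes well beyond all-cause mortality. Section 2 includes the association of "ever or never having attended DSME on major adverse cardiovascular events", and Section 3.4 lists cause-specific admission and death clusters that include MI, stroke, cancer, renal, liver and respiratory disease.

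**The concern.** A summed index treats patients with the same total as alike. For death from any cause that is what the index was built to do. For a stroke or MACE model, a patient with an earlier stroke and a patient with an unrelated condition of equal weight receive the same adjustment, although their risk of the outcome may differ greatly. The same applies to cancer history in the cancer clusters and renal history in the renal cluster.

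If attenders and non-attenders at the same score differ in how often they have had the disease in question, part of that difference would appear as an effect of DSME, in either direction. The authors know this kind of imbalance: the Introduction notes that non-attenders in an earlier cohort of elderly patients "had an increased stroke prevalence, higher diastolic blood pressure" and says that this could explain their higher mortality.

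**Working it through.** The plan gives no figure for residual confounding and no comorbidity prevalence by group, so there is no figure of its own to reproduce. The detectable difference in Section 3.5 plays no part here.

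**Step 1: where disease history could be controlled.**
- Matching (Sections 3.3 and 3.6): age, sex, age at diagnosis, diabetes duration. No disease history.
- Entry: no exclusion for earlier MI, stroke, cancer or renal disease. Section 3.2 sets aside hospitalisations and deaths in the first 12 months after diagnosis, which does not remove earlier or later history.
- Adjustment (Section 3.6): CCI is the only comorbidity term.
- Secondary analysis (Section 3.7): a fuller confounder list is mentioned, but no disease-history term is named.

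**Step 2: the mechanism.** Assume two conditions A and B of equal weight, with score S = A + B, and a true DSME ratio of 1.00. A multiplies the outcome rate by R_A and B by R_B. The article does not list the CCI weights, so equal weight is an assumption. At score 1 each patient has either A or B. With R_B = 1, the ever/never ratio at that score is

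[1 + (R_A − 1)·p_ever] / [1 + (R_A − 1)·p_never],

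where p is the share with A at that score. It equals 1 only if the mix is the same in both groups.

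**Step 3: one case worked through (all inputs assumed).** R_A = 3, R_B = 1; A 10% in ever and 15% in never; B 20% in both; A and B independent. Expected events are in units of the baseline rate.

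| Score | Ever: share | Ever: events | Never: share | Never: events |
|---|---|---|---|---|
| 0 | 0.72 | 0.72 | 0.68 | 0.68 |
| 1 | 0.26 | 0.42 | 0.29 | 0.53 |
| 2 | 0.02 | 0.06 | 0.03 | 0.09 |

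- Crude ratio: 1.20 / 1.30 = 0.923.
- At score 1: (0.42/0.26) / (0.53/0.29) = 1.615 / 1.828 = 0.884.
- Mantel-Haenszel ratio over score: (0.3497 + 0.2215 + 0.0360) / (0.3497 + 0.2505 + 0.0360) = 0.6072 / 0.6362 = 0.954.

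The score removes part of the bias but not all. Adding an indicator for A beside the score identifies both conditions here and returns 1.00.

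**Step 4: range of assumed cases.** Never group A 15%, B 20%; R_A 2 to 4; R_B 1.0 to 1.3; true ratio 1.00.

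| Ever group | Crude | Score-adjusted |
|---|---|---|
| A 12%, B 16% (both 20% rarer) | 0.93–0.97 | 1.00 |
| A 10%, B 15% (both 5 points rarer) | 0.88–0.96 | 0.99–1.00 |
| A 10%, B 20% (only A rarer) | 0.90–0.96 | 0.94–0.98 |
| A 8%, B 20% (only A rarer) | 0.86–0.94 | 0.91–0.98 |
| A 15%, B 15% (only B rarer) | 0.99–1.00 | 1.01–1.05 |

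With A and B entered separately the ratio is 1.00 in every row by construction.

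**Step 5: could such a ratio reach significance?** Take 21,398 attenders (Section 3.5) and assume 5 full years at 0.024 events per year: 21,398 × (1 − e^(−0.12)) ≈ 2,400 attender events. The standard error of the log ratio is about √(1/2,400 + 1/2,400) = 0.029 with one control per attender and √(1/2,400 + 1/9,600) = 0.023 with four. A spurious ratio of 0.95 (log −0.051) gives |z| of about 1.8 and about 2.3. A ratio of 0.98 (log −0.020) gives about 0.7 and 0.9. The matching ratio is not stated, and shorter follow-up lowers these values.

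**The case against.** Several points on the other side stand. CCI does adjust for overall comorbidity burden, and SBP, lipids, smoking, BMI and HbA1c may capture some vascular risk. If attenders are simply healthier across the board, the sum works well, as the first two rows of the Step 4 table show. The stated hypotheses concern all-cause admissions and mortality, and for all-cause mortality a mortality score is a sensible adjuster. Section 4.1 concedes residual confounding in general terms. Section 3.7's fuller confounder list may hold more than the article names, although no disease history is mentioned.

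A reader might infer that every model stays confounded by earlier disease and that DSME will be credited with events it did not prevent. The documents do not support that. They give no data on the mix of conditions at a given score, and the bias can be nil or can run against DSME. A reader might also see a contradiction between the Introduction's remark on stroke imbalance and the adjustment set. That goes too far: the outcome of that study was mortality, where CCI fits best, and this plan adds deprivation, SBP and lipids.

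What remains is that the covariate set is stated for all models and contains no term for history of the outcome disease. A general caveat does not replace adjusting for a diagnosis that is available.

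**Conclusion.** The point holds for 3P-MACE and the cause-specific admission and death models, as possible rather than demonstrated residual confounding. It is a stated analysis choice, not a detail left to another document. Size and direction cannot be determined from the protocol article. Under the assumed prevalences, rate ratios and equal weights, the adjusted ratio with no true effect lay between about 0.91 and 1.05, and at 1.00 when the conditions differed proportionally between groups. That illustration omits the other covariates, so it indicates the mechanism and is not a forecast. The case does not extend to removing CCI from the all-cause models. This is a worthwhile, inexpensive improvement and not a flaw that invalidates the plan.

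**What to change.** In Section 3.6, keep CCI in the a priori set for the all-cause models. For 3P-MACE and for each cause-specific outcome with a corresponding CCI component, add a baseline indicator for history of that condition: prior MI and prior stroke for MACE, and cancer, renal, liver or respiratory history for those clusters. Take these from the CPRD Aurum diagnoses already used to compute CCI; no look-back into hospital records is needed. As a sensitivity analysis, enter the CCI component conditions separately in place of the sum.

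The cost is a few extra degrees of freedom and a little more analysis work. Stating the terms now also avoids adding them after results are known.

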### Plans for addressing missing data

3.7

Assessment of data quality and completeness in CPRD Aurum suggests that correctness of type 2 diabetes is high (94%–98%) indicating that a diagnosis code if found is likely to be correct and there are likely very few patients with type 2 diabetes in the absence of a code.^37^ In our primary analysis, we will use a complete‐case approach based on the main potential confounders listed. We will conduct secondary analyses using complete cases for the full list of potential confounders, including those expected to have a high proportion of missing data which we do not expect to be missing at random.

CCI will be used to calculate an individual's 10‐year risk of mortality. As it cannot be assumed that covariate measurements (CCI, ever or never attended DSME, diagnostic codes) are missing at random we will not use multiple imputation for these measures.

Data will be recorded as missing where there is no record within 12 months of baseline. Depending on completeness of data a decision will be made on whether to use multiple imputation to manage covariates. As HbA1c, lipids and BP measures are amongst the nine key care processes^5^ completed within primary care every 12 months and linked to the GP Quality Outcome Framework, it is likely these are well completed with the dataset.

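### The secondary complete-case analysis changes covariates and patients in one step, so its difference from the primary estimate cannot be attributed to either

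*Protocol article*

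**What the plan says.** Section 3.7 fixes two analysis sets. For the first: "In our primary analysis, we will use a complete‐case approach based on the main potential confounders listed". For the second it plans "secondary analyses using complete cases for the full list of potential confounders, including those expected to have a high proportion of missing data", and it adds that these values are not expected to be missing at random. The rule for a missing value is: "Data will be recorded as missing where there is no record within 12 months of baseline".

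Imputation is left open: "Depending on completeness of data a decision will be made on whether to use multiple imputation to manage covariates". For comorbidity index, DSME status and diagnostic codes it is ruled out, since the article does not assume that they "are missing at random we will not use multiple imputation for these measures".

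The covariates are described in three places:

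- Section 3.4 gives the main confounders as age, sex, time since first diagnosis code, comorbidity index, BMI, smoking, HbA1c, systolic pressure and total cholesterol. Ethnicity and deprivation are added after linkage.
- Section 3.6 states one set for everything: "All models will be adjusted a priori for CCI, IMD, HbA1c, BMI, smoking status, lipid level and SBP". Ethnicity is not in it.
- Section 3.7 refers to a main list and a longer full list, and does not set out the full list.

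**The concern.** In an observational comparison of attenders with non-attenders, confounding is the main threat, and an analysis with more confounders will naturally be set beside the primary one. Here the added covariates also decide who is analysed. The article itself expects them to be missing often and not at random, so the second set may be much smaller than the first and differently composed.

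If the two hazard ratios differ, either cause could explain it. If they agree, a shift from selection may have offset a shift from adjustment. In both cases the secondary analysis cannot tell the reader what more adjustment did to the DSME estimate.

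**Working it through.** **Inputs.** The article gives no missingness rate for any covariate, so it has no figure to reproduce here. Its one design figure, the detectable difference of about 1.9% in section 3.5, has no bearing on the point. What follows is an illustration with assumed values.

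**Assumptions.** 400,000 patients per scenario, Poisson event rates, true DSME rate ratio 0.90. An added covariate C is present in 40%. An unmeasured severity U is present in 30% and multiplies the rate by exp(0.7) = 2.01. Where C confounds, it multiplies the rate by exp(0.6) = 1.82 and lowers the log-odds of attendance by 0.8. Rate ratios are used so that non-collapsibility does not enter.

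**Three fits.** (a) without C, all patients; (b) without C, only patients with C recorded; (c) with C, the same patients as (b). The plan supplies the counterparts of (a) and (c). It does not supply (b).

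| Scenario | (a) | (b) | (c) | With C, all patients |
|---|---|---|---|---|
| 1. C confounds; recorded in 60% at random | 0.801 | 0.801 | 0.898 | 0.899 |
| 2. C confounds; recording depends on C only | 0.803 | 0.826 | 0.907 | 0.899 |
| 3. No confounding; recording depends on DSME and U | 0.902 | 0.766 | 0.766 | 0.902 |
| 4. No confounding; recording depends on U, and U modifies the DSME effect | 1.016 | 1.066 | 1.066 | 1.016 |
| 5. C confounds; recording as in 3 | 0.804 | 0.677 | 0.760 | 0.902 |

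Between 55% and 60% of patients remain in (b) and (c), as a result of the recording rates assumed.

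**Hand check of scenario 3.** Attenders are recorded at 70% if not severe and 50% if severe; controls at 40% and 80%.

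- Severe share among recorded attenders: 0.15/(0.15 + 0.49) = 0.234. Mean rate multiplier: 1 + 0.234 × 1.014 = 1.238.
- Severe share among recorded controls: 0.24/(0.24 + 0.28) = 0.462. Mean rate multiplier: 1 + 0.462 × 1.014 = 1.468.
- Ratio: 0.90 × 1.238/1.468 = 0.76, in line with the simulated 0.766.

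**Reading.** From (a) to (c), scenario 1 moves because of adjustment only, and scenarios 3 and 4 because of selection only. Fit (b) separates them: in 1 the whole change lies between (b) and (c), in 3 and 4 between (a) and (b). In scenario 5 the visible change is small, 0.760 − 0.804 = −0.044, but it is the sum of −0.127 from changing patients and +0.083 from adding C.

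**Covariate lists side by side.** If deprivation and ethnicity belong to the main list, the article names no further covariate for the full list. If they are the additions, deprivation cannot be one of them in practice, because section 3.6 already puts it in every model, and only ethnicity is left. Neither reading identifies the heavily missing covariates that section 3.7 has in mind.

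**The case against.** The strongest reply is that section 3.7 states nothing false. The refit is a detail that a full protocol or analysis plan may contain, and the article never says that a change between the two analyses will be read as confounding removed. Section 4.1 concedes residual confounding and says causality would need a randomised trial. Imputation also remains possible; if it kept the patients the same in both models, the difficulty would largely go. These points stand and limit the finding. They do not remove it: the article commits to this pair of complete-case analyses, and as committed their difference cannot be interpreted.

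A reader might go further and infer that the secondary analysis would be biased towards benefit. One can build such a case: no DSME effect, 30% of patients ill, attenders recorded regardless of health, controls recorded at 30% if well and 70% if ill. The ill share among recorded controls is then 0.21/0.42 = 0.50, and the hazard ratio is 1.15/1.25 = 0.92 if illness carries a hazard ratio of 1.5, or 1.45/1.75 = 0.83 at 2.5. The documents do not support that inference, for three reasons:

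- The calculation leaves illness unadjusted and compares with a fully observed cohort. The plan adjusts for comorbidity and risk factors, and its primary analysis is itself complete-case.
- The idea that attenders are monitored more, and ill controls measured more, mostly describes HbA1c, blood pressure, cholesterol and BMI. These are on the main list, and section 3.7 expects HbA1c, lipids and blood pressure to be well recorded. For ethnicity and socio-economic data, section 4.1 expects linkage largely to fill the gaps.
- Values missing not at random do not by themselves bias a complete-case model. In scenario 2, (c) is 0.907 against 0.899.

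A reader might also see a flat contradiction between sections 3.6 and 3.7. The set in 3.6 can be read as a minimum, so what remains is unclear list membership.

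**Conclusion.** The point holds as one of attribution. Section 3.7 changes covariates and patients together, using covariates it expects to be heavily and non-randomly missing, and offers nothing to separate the two effects. Bias in either analysis is not demonstrated.

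The size in this study is unknown. The simulated values rest wholly on assumed recording rates and effects, and they treat the first analysis as fully observed, which the planned primary analysis is not. They show that the ambiguity is possible in either direction, and are no forecast. The unclear membership of the main and full lists rests on the text alone and needs no assumption. Given how little the remedy costs, the change should be made.

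**What to change.** In section 3.7, add a refit of the main-list model on exactly the patients in the full-list complete-case set, and report three estimates together for each outcome: primary, refit, full list. Read primary against refit as the effect of changing patients, and refit against full list as the effect of added adjustment. State that a hazard ratio is non-collapsible, so the second step can include some change that is not confounding. The split is also an accounting one: in scenario 2 part of the first step arises because C confounds less among the patients retained.

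Then write out the main and the full list by name, placing deprivation and ethnicity, and bring sections 3.4, 3.6 and 3.7 into line.

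The cost is one extra model per outcome, a sentence in section 3.7 and a short covariate list. No new data are needed.

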**Methods and Analysis:**

This protocol details a 10‐year retrospective open cohort study of patients aged over 18 years old who have a clinical diagnosis of type 2 diabetes and were registered to an English GP practice from 29 March 2011 to 29 March 2021 and have attended DSME. Patients in the '*ever*' cohort will be matched at baseline for age, sex, age at diagnosis and diabetes duration, to those who have '*never*' attended DSME. Data will be identified via the UK Clinical Practice Research Datalink and linked to Hospital Episode Statistics Admitted Patient Care data, Office for National Statistics death registrations and patient Index of Multiple Deprivation deciles. Patients will be followed‐up through serial cross‐sections. Multiple imputation will be considered to manage covariates where data are >12‐months from baseline or are not expected to be missing at random. Cox proportional hazard regression and time to event modelling adjusted a priori for cofounding during multivariate analysis will be used.

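### The abstract and section 3.7 give opposite imputation rules for data not missing at random, and the 12-month covariate window has no direction, so post-DSME values can count as baseline

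*Protocol article*

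**What the plan says.** **Imputation.** The abstract (Methods and Analysis) names two situations in which multiple imputation may be used for covariates: the data lie more than 12 months from baseline, "or are not expected to be missing at random".

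Section 3.7 names three items ("CCI, ever or never attended DSME, diagnostic codes") and says that, because one cannot presume they "are missing at random we will not use multiple imputation for these measures". The main analysis is fixed: "In our primary analysis, we will use a complete‐case approach based on the main potential confounders listed". Secondary analyses are also complete-case, on the full covariate list, "including those expected to have a high proportion of missing data which we do not expect to be missing at random". For covariates in general the matter stays open: "Depending on completeness of data a decision will be made on whether to use multiple imputation to manage covariates". No completeness threshold is given.

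**Window.** Section 3.7 states: "Data will be recorded as missing where there is no record within" 12 months of baseline. Section 3.3 sets baseline, for attenders and their matched controls, at the date of the DSME intervention. Section 3.6 adjusts every model for CCI, IMD, HbA1c, BMI, smoking, lipids and SBP. The Discussion (section 4) says that DSME improves short-term HbA1c.

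**The concern.** There are two separate faults in stated rules, and a smaller ambiguity.

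First, the abstract treats not being missing at random as a reason to consider imputation, and section 3.7 treats it as a reason against. Standard multiple imputation fills gaps from the observed data on the assumption that, given those data, missingness does not depend on the unseen value. Where that is not believed, imputation needs an explicit model for the departure, and the article names none. An analyst working from the abstract would impute the covariates for which the standard method is least justified.

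Second, a window with no direction around the exposure date lets a consequence of exposure into the adjustment set. If an attender's HbA1c is measured some months after the course, it may already carry the course's effect. Adjusting for it compares attenders and controls at equal post-course HbA1c, which removes whatever part of the effect on admissions or death runs through glycaemic control. A control's value after the matched date carries no such effect, so the covariate no longer means the same thing in the two groups.

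Third, the window sentence does not say which covariates it governs.

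**Working it through.** The plan states no figure on this point, so the check is a comparison of passages.

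1. **Imputation rule.**
   - Abstract: not expected to be missing at random → imputation considered.
   - Section 3.7, CCI, DSME status and diagnostic codes: missing at random cannot be presumed → no imputation.
   - Section 3.7, other covariates not expected to be missing at random → complete-case secondary analysis.
   - Section 3.7, covariates generally → decision deferred until completeness is known.

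   The same property leads to opposite actions. The deferred decision does not resolve this, since it turns on completeness and not on the missingness mechanism.

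2. **Window.**
   - Baseline = DSME date (section 3.3).
   - Eligible record = any within 12 months of baseline, direction unstated (section 3.7).
   - Read as written, eligible dates therefore run from 12 months before DSME to 12 months after it.
   - HbA1c, BMI, SBP and lipids are in every model (section 3.6).
   - DSME changes short-term HbA1c (section 4).

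   Together these allow a post-exposure value of a variable that the article says DSME affects to be adjusted for as baseline. For BMI, SBP and lipids the timing problem is the same, but the article's explicit statement of an effect concerns HbA1c.

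3. **Reach.** The sentence speaks of data without exception, and the abstract applies a 12-month limit to covariates. Read literally, it could reach a CCI diagnosis coded more than a year earlier. The following text in the same paragraph names only HbA1c, lipids and blood pressure.

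4. **Scale of complete-case loss (illustration on assumed rates).** Assume 10% missing in each of four measurements (HbA1c, BMI, SBP, cholesterol).
   - Independent missingness: 0.90^4 = 0.656, so about 66% of patients are retained.
   - Fully overlapping missingness: 1 − 0.10 = 0.90, so 90% are retained.

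   This shows only how much depends on the overlap. The document supplies neither the rate nor the overlap.

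**The case against.** **The contradiction is narrow.** The abstract only says that imputation may be used, section 3.7's ban is tied to three named items, and the primary analysis is complete-case in any event. This stands in part. A reader might infer that the conflict changes the primary estimate. It does not; it affects whether, and for which covariates, an imputed analysis is run. It is still a conflict between stated rules.

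**The window is not stated to be two-sided.** Sections 3.4 and 3.6 speak of confounders and covariates at baseline, and look-back detail is often left to a fuller document. It is true that the plan permits post-DSME values without requiring them, and a reader should not infer that it intends to use them. But the article does state a window rule, and that rule taken at its word admits them.

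**Lifetime covariates.** A reader might infer that everyone whose comorbidity code is over a year old, or who has no such code, is dropped from the primary analysis. The documents do not support this. CCI has its own paragraph in section 3.7, section 3.4 sets no look-back limit for it, and the examples beside the window rule are all repeated measurements. Ethnicity comes by linkage and is not in section 3.6's adjustment list. Smoking status changes over time, so a recency limit for it is a legitimate choice. Only the call to clarify the rule's scope survives.

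**Sample loss.** A reader might also expect a firm figure for patients or matched pairs lost. With no missingness rates and no matching ratio in the document, none can be given. Section 3.7 moreover expects HbA1c, lipids and blood pressure to be well completed.

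**Conclusion.** The point holds in two parts. The abstract and section 3.7 contradict each other on imputing covariates not missing at random, and the abstract's version is unsound for standard multiple imputation. The 12-month rule, as written, allows measurements made after DSME to enter every model as baseline confounders. That could remove part of the effect under study, and unlike the first part it touches the primary analysis.

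The amount of effect removed cannot be stated. It depends on how often the chosen value falls after DSME, and on how much of any benefit runs through the adjusted measurements; the article gives neither. The scope of the rule with respect to CCI is an ambiguity to clear up, not a demonstrated error. These changes should be made before analysis, but they do not call the design into question.

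**What to change.** 1. Delete "or are not expected to be missing at random" from the abstract, so that one imputation rule applies in both places.
2. In section 3.7, limit the window for HbA1c, SBP, cholesterol and BMI to the 12 months up to and including the index date, for attenders and controls alike.
3. State that CCI uses all recorded history up to the index date, with no code counted as zero.
4. If imputation is used for the measured covariates, run it under missing at random, with exposure and outcome in the imputation model, as a sensitivity analysis beside the complete-case primary analysis. Take that decision before outcomes are seen.

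**Cost.** Items 1 to 3 are wording. Item 4, if used, adds moderate computing. The one real downside is slightly more missing values once records made after DSME no longer qualify.
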